
**Table 1 Tab1:**
[figure not shown]
Overview of enrollment, assessment, and evaluation of the LIPSY-trial

### Participant timeline and recruitment

Potential participants will be recruited through the Jobcenter Leipzig in the months previous to the intervention, where they will receive a screening test that will be used to identify potential participants that receive means-tested benefits and suffer from a mental health problem. If tested positive in the screening, they will receive a detailed information sheet on the goals, nature, and implications of the trial as well as on data protection regulations and will be asked to sign a consent form. Potential study participants will be given sufficient time to consider their participation and to ask questions. The psychologists that are responsible for the first assessment in the trial are directly located in the job center to reduce the threshold for participation. Due to the sustained Covid-19 pandemic, we will also consider alternative ways of recruiting, e.g., via written invitations and directly at the clinic. We are planning to start the intervention with the first participants in April 2021 and to include the last participant in December 2022. Since IPS is highly individualized and need-oriented, there are no strict time schedules for the intervention, and IPS may be going on even after the project is finished. Enrolled participants will be assessed at baseline (t0) and after 6 (t1), 12 (t2), and 18 months (t3). We offer the possibility to partake in a project that is aimed at improving the situation of our target group and where participants receive support that can help them to better find work and improve their mental health which we expect to promote participant motivation and retention. Figure 1 shows the flow of participants in the LIPSY trial.

**Fig. 1 Fig1:**
[figure not shown]
Flow of participants in the LIPSY-Trial (TAU = treatment-as-usual, IPS = Individual Placement and Support)

### Sample size

Sample size calculation is based on the primary outcome measure (competitive employment for at least 1 day). In the IPS-literature there is only one European Trial with data from a German study center [12]. The proportions of the EQOLISE-Trial were applied in the power calculation (IG: 0.55, CG: 0.28). To detect a between-group effect of ∆ = 0.27 in favor of IG at 18 months, considering a significance level of α = 0.05 (one-sided) and a statistical power of 1 - β = 0.80, we estimated a target sample of *n* = 41 participants per arm is needed. Anticipating a drop-out rate of 30% until 18 months after baseline assessment based on experiences with previous clinical research projects, the total sample size would have to comprise roughly 60 individuals per group.

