### Statistical methods

All data will be examined with regard to potential inconsistencies and missing values. Missing information in variables will be inspected and addressed by using multiple imputation methods [43], if appropriate. In order to check for systematic differences between completers and non-completers we will perform a dropout analysis. In addition, we will check if there are systematic differences between IG and active CG with regard to sociodemographic, health-related and employment variables. Analyses on primary and secondary outcomes will be performed as intention-to-treat. In addition, we will also perform a “per-protocol”-analysis including all participants from the IG that completed the goal agreement and their first intervention and participants from the active CG. Treatment effects on primary and secondary outcomes will be tested using appropriate panel-data regression models including group, time, an interaction between group and time as predictors and adjusting for relevant covariates and baseline outcome measures. Acceptability, uptake and adherence with regard to the intervention will be evaluated using descriptive statistics.

For all analyses the level of statistical significance will be set to *p* < .05. The results of the study will be reported according to the guidelines of *the Consolidated Standards of Reporting Trials* (*CONSORT*) statement [44].

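### The 80% power holds only for a one-sided 5% test, and the analysis section does not say whether the primary test is one-sided or two-sided

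*Protocol article*

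**What the plan says.** The Protocol article, Sample size, bases the calculation on the binary primary outcome at 18 months. It takes rates of 0.55 (IPS) and 0.28 (control) from an earlier European trial, "considering a significance level of α = 0.05 (one-sided) and a statistical power of 1 - β = 0.80". The result is that "41 participants per arm is needed". With 30% dropout by 18 months, "the total sample size would have to comprise roughly 60 individuals per group".

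The Statistical methods section gives one decision rule: "For all analyses the level of statistical significance will be set to" p < .05. It covers the primary and secondary outcomes alike and mentions neither one-sided nor two-sided testing.

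The Objectives section states a directional hypothesis for the primary outcome, namely that IPS is superior to the control condition. It names no test. For the other vocational and health outcomes it announces an analysis of effects without a direction.

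The one-sided level appears only in the Sample size section, and no reason is given for it.

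**The concern.** A one-sided and a two-sided test at 5% are different tests, with different critical values, power and error rates. The plan sizes the trial on one of them and then states a general threshold that does not say which applies to the primary outcome.

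Each reading has a consequence that the article does not state. Under a two-sided reading, the trial has less than the advertised power at the planned size. Under a one-sided reading, the superiority claim carries a 5% false-positive risk rather than the 2.5% in that direction from a two-sided 5% test.

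The practical risk lies in results that favour IPS with a two-sided p between 0.05 and 0.10. Such a result is significant on one reading and not on the other, and the analysis section does not settle which verdict applies before the data are seen.

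**Working it through.** **Inputs, all from Sample size:** p1 = 0.55, p2 = 0.28, difference 0.27, α = 0.05 one-sided, power 0.80, dropout 30%, about 60 randomised per arm. Allocation is 1:1 (Assignment of interventions).

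**Formula** (two proportions, pooled variance under the null, no continuity correction):

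n per arm = [z_α·√(2p̄(1−p̄)) + z_β·√(p1(1−p1) + p2(1−p2))]² / (p1−p2)²

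- p̄ = (0.55 + 0.28)/2 = 0.415, so √(2 × 0.415 × 0.585) = √0.48555 = 0.6968
- √(0.2475 + 0.2016) = √0.4491 = 0.6701
- z_β = 0.8416, so the second term is 0.5640

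**Step 1: reproduce the plan (one-sided, z_α = 1.6449).** n = (1.1462 + 0.5640)² / 0.0729 = 40.1, rounded up to 41. Dropout: 41/0.7 = 58.6, so 59, in line with roughly 60. The stated size reproduces, and power at 41 per arm is 80.8%.

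**Step 2: the same inputs two-sided (z_α = 1.9600).** n = (1.3657 + 0.5640)² / 0.0729 = 51.1, rounded up to 52. Dropout: 52/0.7 = 74.3, so 75 per arm, or 150 in total.

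**Step 3: power at the planned size.** Completers: 60 × 0.7 = 42 per arm. Power = Φ[(0.27·√n − z_α × 0.6968)/0.6701].

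- Two-sided, n = 42: Φ[(1.7498 − 1.3657)/0.6701] = Φ(0.573) = 0.717
- One-sided, n = 42: Φ[(1.7498 − 1.1462)/0.6701] = Φ(0.901) = 0.816
- Two-sided, n = 60 (outcome obtained for everyone): Φ[(2.0914 − 1.3657)/0.6701] = Φ(1.083) = 0.861

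**Step 4: sensitivity to the method, two-sided 5%.**

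| Method | 41 per arm | 42 per arm |
|---|---|---|
| Pooled normal approximation | 70.6% | 71.7% |
| Arcsine | 71.1% | 72.1% |
| Exact enumeration of the z test | 72.8% | 74.5% |
| Fisher's exact test | 64.7% | 66.7% |

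Every method puts two-sided power below 80% at the planned number of completers.

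**Step 5: size of the disputed zone.** Under the planning rates, the probability of a result that is significant one-sided but not two-sided at 42 per arm is 0.816 − 0.717 = 0.099 by the pooled formula, and 0.814 − 0.745 = 0.069 by exact enumeration.

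**The case against.** The best defence is that the article can be read as one coherent plan. Objectives states a directional hypothesis, Sample size openly declares a one-sided 5% level, and Statistical methods uses the same 0.05. On that reading nothing conflicts, the 80% is right, and the sidedness of the test is a detail that a separate analysis plan may settle.

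Much of this stands. A reader might infer that the sample size is miscalculated or that the stated power is wrong. The documents do not support that: on its declared one-sided basis the calculation is correct. A reader might also infer that the analysis section prescribes two-sided testing and so contradicts the sample size. It does not say two-sided. Nor can one rely on software printing two-sided p-values, since these convert directly when the effect lies in the hypothesised direction.

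It is also fair that the 72% is not a prediction for the planned analysis. It is a two-proportion approximation for completers, whereas the plan foresees covariate-adjusted panel regression, intention-to-treat analysis and multiple imputation where appropriate.

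What does not stand is that this is only omitted detail. The article fixes a sidedness for planning and then fixes a general threshold that does not carry it forward. That threshold also governs secondary outcomes for which no direction is stated, so it cannot plainly mean one-sided throughout. If the primary test is the exception, the exception has to be stated. A later analysis plan cannot settle it without consequence: two-sided testing would make the published 80% inapplicable, and one-sided testing would confirm a 5% directional error rate that has not been justified.

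**Conclusion.** The concern holds as an unresolved ambiguity in the primary decision rule, not as an arithmetical error or a direct contradiction.

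- **Read two-sided at 5%:** about 72% power (pooled) to 75% (exact) with 42 completers per arm, against the stated 80%. Power is about 86% if the outcome is obtained for all 60 per arm.
- **Read one-sided at 5%:** the stated power stands, but the chance of falsely declaring IPS superior is 5% instead of 2.5%, with no reason given.

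These figures assume the plan's own rates of 55% and 28%, 60 randomised per arm, 30% loss and an unadjusted comparison of two proportions. The shortfall below 80% depends on both the two-sided reading and substantial loss: 52 of 60 completers per arm (8/60, about 13% loss) would already reach 80% two-sided. The ambiguity about the verdict does not depend on dropout.

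**What to change.** Before unblinding, make two changes.

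1. In Statistical methods, state the sidedness of the primary test. Two-sided 5% with a 95% confidence interval is preferable.
2. In Sample size, restate the power to match: with 120 randomised and 30% dropout, about 72–75% for 55% against 28%, and about 86% if the outcome is obtained for everyone.

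If one-sided 5% is kept, say in Statistical methods that it applies to the primary test, justify it, and report the matching 90% confidence interval.

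The cost is about two sentences and, under the preferred option, a less favourable published power. No added enrolment is asked for. Holding 80% power two-sided with 30% dropout would take 75 per arm, so keeping 60 means openly accepting the lower figure.

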### Assignment of interventions: allocation and blinding

Eligible persons who consented to participate will be randomly assigned to either IG or active CG using a computerized random number generator. A block-randomization algorithm with a targeted assignment ratio of 1:1 for participants in IG or active CG will be used, stratified by sex and three age groups: 18–35, 36–50, 51+. This facilitates balance between study arms in both sample size and basic demographic variables. Stratified randomization will be achieved by using a separate randomization procedure within each of the strata.

Blinded randomization will be done by an independent statistician, generating randomization block lists with respective statistics software. The randomization lists (one for each stratum) will be concealed to the study coordinator and recruiting staff members with regard to the lists’ strata identity. Employees at job center and clinic who recruit eligible participants and collect data, will remain blind to the group allocation. Participants of both IG and active CG cannot be blinded to the intervention they receive, because blinding is per se not possible when conducting an IPS intervention. However, the statistician analyzing the data and staff members evaluating the results will remain blind to the group allocation.

An independent researcher will generate the allocation sequence. Psychologists from the clinic will enroll participants and inform the researchers about the enrollment who will then initiate randomization and assign the participants to one of the groups.

### Data collection and management

Baseline assessments will be conducted using written questionnaires handed out to participants at t0. Follow-up assessments (t1 - t3) will be scheduled 6, 12, and 18 months after the baseline assessment, and participants will be invited to fill out the questionnaires in the presence of project staff, so that they can ask for support or clarification if they wish to. In addition, we plan to include register data from the job center on the current working status of participants at t3. An overview of all instruments utilized in the trial can be found in Table 1.

Multiple processes will ensure a high level of data quality. Instruments and items were selected by expert researchers, and assistants will be present when participants are filling out the questionnaires, to answer questions and/ or support participants. In addition, data will be quality checked at the research team on a regular basis which includes the checking of adherence to inclusion criteria and checking the completeness and plausibility of data as well associated study documents like the consent form. Data auditing will be administered in form of reviews of the data collection across baseline and three follow-up assessments. The research team will monitor data and document serious adverse events.

The data monitoring committee for the trial (DMC) consists of three well-established, expert researchers that are independent from our funding institution and do not have competing interests: [name]. [name] (University of Applied Sciences Mittweida), [name]. [name] (Leipzig University), and [name]. [name] (University Medical Center Hamburg-Eppendorf). The research team will report to the DMC on a regular basis, and the DMC will be involved in the planning, implementation, evaluation, and monitoring of the trial.

We expect to create higher rates of questionnaire returns in the follow-ups by providing assistants that can support participants that have questions regarding the questionnaires.

The collection, storage, and analysis of study data will be carried out in compliance with the relevant data-protection regulations, especially the *DSGVO*. Collected data will be entered in a database using a statistics software package (Stata) and stored locally and password protected. To ensure completeness and accuracy of data entry, a double entry check will be performed. Each participant will receive a pseudonym (project-ID) that will allow us to connect data from different time points and to integrate data from the clinic. The document that connects personal data and project-IDs will be password protected, stored separately from the data, and destroyed at the end of the study. This allows entering and analyzing the collected data in a strictly pseudonymous form. Results will be published in anonymous form, and data will be archived on servers at the University of Leipzig. The research team and the members of the study group at the clinic will have access to the final trial data set.

No interim analyses are planned.

### Adverse events

The participants will be requested to immediately inform their coaches/ hospital staff about serious adverse events, and the occurrence of serious adverse events will be documented. The risk for the occurrence of adverse events through study participation is estimated to be minimal.

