### Interventions

Participants from both groups will receive high-quality TAU, i.e. the standard treatment according to their needs by a multiprofessional team at the outpatient psychiatric clinic. This can include medication, psychotherapy and a wide set of optional psychosocial therapies, like social skills training. In addition, participants in the IG will receive IPS, and participants in the active CG will receive a booklet that gives an overview on measures for vocational rehabilitation. There are no restrictions with regard to concomitant care.

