#### Intervention group

IPS coaching is focused on the individual needs and goals of participants, and it covers all phases of vocational orientation and goal development, job application, beginning to work, workplace adaption, job retention, job loss, and (re)orientation. If they want to, participants can involve a related person and/or their employers in the coaching process, and coaches can meet participants outside the hospital. In addition, coaches build up contacts to potential employers in general. There will be a basic documentation of meetings, talks and communication between coaches and participants including key issues and agreements. All coaches are part of the clinic team, received an online training with certification (https://ipsworks.org/index.php/training-courses/), and they work manual-based [19]. Coaches cooperate closely with physicians, social workers, and therapists.

The coaching starts with a planning phase in which the needs of participants are assessed in detail and personal goals are defined. Specific questionnaires can be used to explore potential goals, strengths, and experiences of participants; they may also address cognitive abilities, social competence, qualifications, and daily activities, depending on the needs of the participants. Besides starting a job or changing occupations the exploration may also yield other goals like the acquisition of new qualifications, the beginning of studies, or an apprenticeship. Goals will be written down in an objective agreement which includes statements on vocational preferences, companies that will be addressed, and participant’s needs.

In the intervention phase, goal achievement will be addressed, for example, employers could be contacted. It is important that the intervention phase starts early, best in the first 30 days after the beginning of the coaching process. Once the participant has managed to start work/ training/ studies (integration phase), the coaching will be adapted to this new situation. For example, job coaches can then give the following support: meeting with family members to explore job-related strengths and goals; meeting with job center staff to coordinate planning; job search and preparation of job interviews; time management; social skills training; communication with the employer, e.g., for conflict mediation or workplace adaption; workplace coaching; group sessions with other participants.

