The productive contact with employers is a crucial success factor. Therefore, it will be discussed at an early stage if, and in which form, it could make sense for participants to reveal their illness to their potential employer. Participants’ preferences with regard to the disclosure of their mental health status by their coach to a potential employer will be documented and binding. If a participant decides to disclose their condition, the contact between coach and employer will be documented. The participant can withdraw their agreement at any time.

Participants will be coached steadily, if requested also after the project has ended. Continued support via the hospital’s own social services is available. Due to the close contact between coach and participant, potential barriers can be identified at an early stage and individual solutions can be developed. Should participants miss appointments or not follow agreements, coaches will actively seek contact for 8 weeks after the last contact. Participants can withdraw from the program at any time. In addition, the IPS-process includes multiple opportunities for participants to give feedback and shape the process, which are expected to contribute to intervention adherence.

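### The stated route for reporting serious adverse events gives the intervention arm a channel that the control arm lacks; the same scheduled enquiry in both arms would be a cheap improvement

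*Protocol article*

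**What the plan says.** The Adverse events section sets out a route that starts with the participant: "The participants will be requested to immediately inform their coaches/ hospital staff about serious adverse events, and the occurrence of serious adverse events will be" […]. The sentence ends by saying that these events are put on record, and the section adds that the risk from taking part is judged minimal.

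The Interventions section separates the arms: "participants in the IG will receive IPS, and participants in the active CG will receive a booklet". It also describes what they share: "Participants from both groups will receive high-quality TAU, i.e. the standard treatment according to their needs by a multiprofessional team at the outpatient psychiatric clinic".

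The Intervention group section says of the coaches: "All coaches are part of the clinic team". On their records it says: "There will be a basic documentation of meetings, talks and communication between coaches and participants including key issues and agreements". Coaches may meet participants outside the hospital, coaching is continuous, and after missed appointments or broken agreements "coaches will actively seek contact for 8 weeks after the last contact".

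The Data collection and management section adds: "The research team will monitor data and document serious adverse events". It schedules questionnaires at 6, 12 and 18 months with project staff present, and states no difference by arm. The Assessments section lists a shortened FIMPsy that covers hospital stays, also without restriction to one arm. Its time points would be in Table 1, which is not visible in the text at hand.

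**The concern.** Spontaneous reports depend on how often a participant talks to someone who can receive them. The recipients named are coaches and hospital staff, and one of these two exists in one arm only. That recipient also has steady contact, keeps a record of it, and follows up people who go quiet, which is when an admission or a crisis could otherwise go unreported. No similar outreach is described for the control group, whose clinic care is given according to need with no stated minimum of contact.

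If more events are captured in the intervention group, the SAE table can show an excess under IPS that does not exist, or mask a true reduction. Participants are included with GAF ≤ 50, so serious events from the underlying illness are plausible in either arm, and unequal capture would act on those too. The research team reports regularly to the data monitoring committee. If SAEs are tabulated by arm, there or in the publication, readers will compare the columns.

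**Working it through.** **Step 1: the channels, arm by arm.**

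| Source of SAE information | Intervention group | Control group |
|---|---|---|
| Hospital staff (Interventions; Adverse events) | yes | yes |
| Coach as recipient of reports (Adverse events; Intervention group) | yes | no |
| Recorded coach contacts (Intervention group) | yes | no |
| Active outreach for 8 weeks after last contact (Intervention group) | yes | no equivalent described |
| Documentation by the research team (Data collection and management) | yes | yes |
| Questionnaires at t1–t3 (Data collection and management) | yes | yes |
| FIMPsy hospital stays (Assessments; time points not visible) | no arm restriction stated | no arm restriction stated |

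The arms differ only through the coach, and always in the direction of more contact in the intervention group. The shared rows limit the difference but do not remove it. Documentation by the research team concerns recording, not how an event first becomes known. The questionnaires are not described as carrying SAE items, and the article does not link the FIMPsy to SAE reporting.

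**Step 2: what the plan quantifies.** It states no SAE rate and no capture probability, so there is no safety figure to reproduce. The only plan figure used below is about 60 per arm. That follows from the Sample size section: 41 / (1 − 0.30) = 58.6, so 59, given as roughly 60.

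**Step 3: size, under assumptions.** Let p be the true 18-month SAE risk, equal in both arms, and let c_IG and c_CG be the shares captured.

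- Expected participants with a recorded SAE: 60 × p × c
- Apparent risk ratio: (60 × p × c_IG) / (60 × p × c_CG) = c_IG / c_CG

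The ratio depends on neither p nor the sample size. With p = 0.20 (assumed), 60 × 0.20 = 12 participants per arm have a true event:

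| c_IG | c_CG | Recorded IG | Recorded CG | Apparent ratio |
|---|---|---|---|---|
| 0.90 | 0.90 | 10.8 | 10.8 | 1.00 |
| 0.80 | 0.70 | 9.6 | 8.4 | 1.14 |
| 0.90 | 0.70 | 10.8 | 8.4 | 1.29 |
| 0.90 | 0.60 | 10.8 | 7.2 | 1.50 |
| 0.90 | 0.50 | 10.8 | 6.0 | 1.80 |

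All risks and capture rates here are assumed. The first row is as compatible with the document as the last.

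**The case against.** The strongest reply is that the shared routes may do most of the work. Being in treatment at an outpatient psychiatric clinic is an inclusion criterion, both arms see the same clinic team, and the coaches are members of it. The research team documents SAEs without regard to arm, and hospital stays are asked about separately. SAEs are neither a primary nor a secondary outcome, no between-arm test of them is announced, and the risk from participation is stated as minimal. In a trial of this size a modest artefact would also be hard to tell from chance: 11 versus 7 of 60, the 1.50 row rounded, gives a two-sided Fisher p of 0.44. Finally, a condensed article may leave a scheduled SAE enquiry to the full protocol.

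Much of this stands. A reader might infer that SAEs are in fact collected more completely under IPS, or that the arms cannot be compared at all. The document supports neither reading: the hospital-staff route is open to both arms, central documentation is not arm-specific, and the capture rates are unknown. The absence of a scheduled SAE enquiry from the article is not a fault in itself.

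One thing remains, and it is stated, not omitted: the route as written names a recipient that one arm does not have. Coaches' membership of the clinic team does not even this out, since what a coach learns can reach hospital staff for intervention participants only. The stated minimal risk concerns participation and does not cover events arising from the illness. The chance argument limits how firmly an artefact could be read as a signal; it does not make capture equal.

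**Conclusion.** The point holds as a cheap improvement to a stated procedure. SAE counts by arm may be biased towards more recorded events in the intervention group. The direction follows from the extra channel; the size cannot be determined and could be near zero. The assumed scenarios span an apparent ratio from 1.00 to 1.80 with no true difference. The conclusion rests on the Adverse events route being applied as written, and on no matching scheduled enquiry already standing in the full protocol. The primary analysis is not affected.

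**What to change.** - Leave immediate reporting to coaches and hospital staff as it is.
- Add the same few SAE items, covering the time since the last assessment, to the t1, t2 and t3 questionnaires for every participant in both arms.
- Record for each SAE how it became known: scheduled enquiry, coach, hospital staff or other.
- Report all SAEs by arm with their source. Use the events from the common scheduled enquiry as the like-for-like between-arm summary, and keep coach- and staff-reported events in the report.
- Use the FIMPsy hospital-stay items for admissions at those time points where the instrument is given.

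The cost is slightly longer questionnaires at assessments that already take place, and an added sentence or two in the Adverse events section. The limitation should be stated alongside: with 30% drop-out expected by 18 months, a scheduled enquiry misses deaths and other events in people who do not attend. Resting the comparison on it alone would drop those events, together with known coach reports, and could understate harm in the intervention group. It therefore supplements the spontaneous reports and does not replace them. If the full protocol already contains such an enquiry, recording and reporting the source is all that needs adding.
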